# Effect of opposing needling on motor cortex excitability in healthy participants and in patients with post-stroke hemiplegia: study protocol for a single-blind, randomised controlled trial

**DOI:** 10.1186/s13063-021-05443-x

**Published:** 2021-07-22

**Keywords:** Opposing needling, Stroke, Post-stroke hemiplegia, Transcranial magnetic stimulation, Resting motor threshold, Motor-evoked potential

## Abstract

**Background:**

Opposing needling has an obvious curative effect in the treatment of post-stroke hemiplegia; however, the mechanism of the opposing needling in the treatment of post-stroke hemiplegia is still not clear. The purpose of this study is to investigate the effect of opposing needling on the excitability of primary motor cortex (M1) of healthy participants and patients with post-stroke hemiplegia, which may provide insight into the mechanisms of opposing needling in treating post-stroke hemiplegia.

**Methods:**

This will be a single-blind, randomised, sham-controlled trial in which 80 healthy participants and 40 patients with post-stroke hemiplegia will be recruited. Healthy participants will be randomised 1:1:1:1 to the 2-Hz, 50-Hz, 100-Hz, and sham electroacupuncture groups. Patients with post-stroke hemiplegia will be randomised 1:1 to the opposing needling or conventional treatment groups. The M1 will be located in all groups by using neuroimaging-based navigation. The stimulator coil of transcranial magnetic stimulation (TMS) will be moved over the left and right M1 in order to identify the TMS hotspot, followed by a recording of resting motor thresholds (RMTs) and motor-evoked potentials (MEPs) of the thenar muscles induced by TMS before and after the intervention. The primary outcome measure will be the percent change in the RMTs of the thenar muscles at baseline and after the intervention. The secondary outcome measures will be the amplitude (μV) and latency (ms) of the MEPs of the thenar muscles at baseline and after the intervention.

**Discussion:**

The aim of this trial is to explore the effect of opposing needling on the excitability of M1 of healthy participants and patients with post-stroke hemiplegia.

**Trial registration:**

Chinese Clinical Trial Registry ChiCTR1900028138. Registered on 13 December 2019.

**Supplementary Information:**

The online version contains supplementary material available at 10.1186/s13063-021-05443-x.

## Background

According to World Health Organization statistics, stroke is the second highest cause of death and a leading cause of disability worldwide [1]. In the USA, stroke is the fourth position in the leading causes of mortality [2] and a leading cause of serious long-term disability [3]. The total direct annual stroke-associated medical expenses are expected to increase from $71.55 billion to $183.13 billion between 2012 and 2030 [4]. In Australia, there are 27,400 new cases of stroke in 2020. The economic impact of stroke is staggering, causing direct economic costs of $6.2 billion, and premature deaths and welfare losses of $26 billion [5]. In China, according to the Chinese stroke epidemiology survey published in the journal *Circulation* in 2017, the incidence and mortality rates associated with stroke were 246.8/100 000 and 114.8/100 000 person-years, representing approximately 2.4 million new cases each year and approximately 1.1 million deaths each year. Among incident and prevalent strokes, ischemic stroke constituted 69.6% and 77.8% of the cases, respectively [6]. Thus, stroke shows the characteristics of high incidence, high morbidity, and high disability [7–9].

The most effective evidence-based treatment for ischemic stroke is tissue plasminogen activator (tPA) administration within 4.5 h or mechanical thrombectomy (MT) within 6 h, which can salvage the tissue at risk in the penumbra of a brain infarct and reduce further disability if administered promptly after stroke onset [10, 11]. A retrospective cohort study suggested that a shorter time to treatment with tPA was associated with lower all-cause mortality and lower all-cause readmission at 1 year [12]. However, in China, only about 10–20% of ischemic stroke patients arrive at hospitals within 3 h, and less than 3% of stroke patients are treated with tPA [13]. Most ischemic stroke patients are not treated in time, which delays the therapeutic effects, leading to higher mortality and disability rates. For patients with stroke at the convalescence stage, the existing treatments mainly include conventional antiplatelet therapy (monotherapy or combinations of aspirin, clopidogrel, and cilostazol) [14], complementary and alternative medicines (herbal medicine, Chinese conventional exercise therapy, acupuncture, moxibustion, etc.) [15–19], and rehabilitation therapy [20]. Most patients in China with post-stroke hemiplegia are treated with a combination of Chinese and modern medicine. One study recommended acupuncture for patients with various stroke recovery periods [21]. Acupuncture has been used to treat post-stroke hemiplegia for more than 2000 years and has shown significant therapeutic effects [22, 23]. Opposing needling, one of the most common acupuncture treatments for post-stroke hemiplegia, comprising the selection of acupuncture points contralateral to the diseased side [24]. A systematic review suggested that in comparison with ipsilateral acupuncture, opposing needling showed a superior effect on the recovery rate and influence the recovery from post-stroke hemiplegia by improving the motor function of the affected limbs, the daily living ability of the patients, and even neurological deficits [25]. Although opposing needling has obvious curative effects in the treatment of post-stroke hemiplegia, the mechanisms underlying its therapeutic effects remain unclear. The existing research on the mechanisms of opposing needling mainly involved experimental animals, and only a few studies have assessed patients with post-stroke hemiplegia. Thus, with a single-blind, randomised controlled design, this study aims to investigate the effect of electroacupuncture and opposing needling on the excitability of the M1 under physiological and pathological conditions.

## Objectives

The primary objective is to investigate the effect of electroacupuncture on the excitability of the M1 in healthy participants, and then to further investigate the effect of opposing needling on the M1 excitability of patients with post-stroke hemiplegia. Secondary objectives are to explore the optimal frequency of electroacupuncture for motor cortex excitability in healthy participants and explore a potential approach to predict the possibility of recovery in patients with post-stroke hemiplegia.

## Methods/design

### Study design

This will be a single-blind, randomised, sham-controlled trial (RCT) conducted in accordance with the Declaration of Helsinki. This RCT will be conducted at the South China Research Center for Acupuncture and Moxibustion, Guangzhou University of Chinese Medicine and Guangdong 999 Brain Hospital from January 2020 to January 2022. All participants will provide signed informed consent before proceeding with the trial. All study protocols have been reviewed and approved by the China Ethics Committee of Registering Clinical Trials (ChiECRCT20190223). This study has been registered with the Chinese Clinical Trial Registry (ChiCTR1900028138). The protocol follows the Standard Protocol Items: Recommendations for Interventional Trials (SPIRIT) 2013 Statement. The SPIRIT checklist is provided as Additional file 1. The study design is presented in the flowchart in Figs. 1 and 2.

**Fig. 1 Fig1:**
[figure not shown]
Consort flow chart. MMSE, Mini-Mental State Examination; BMI, body mass index; MRI, magnetic resonance imaging; NIHSS, National Institutes of Health stroke scale; FMA, Fugl-Meyer assessment; BI, Barthel index; EA, electroacupuncture; MEP, motor-evoked potential; RMT, resting motor threshold; TMS, transcranial magnetic stimulation; ON, opposing needling; CT, conventional treatment

**Fig. 2 Fig2:**
[figure not shown]
Schematic overview of enrolment, intervention, and assessments

### Recruitment

Recruitment for this RCT will be initiated by posting study recruitment flyers at the Guangzhou University of Chinese Medicine and Guangdong 999 Brain Hospital. Interested patients will be instructed to contact the recruitment staff by telephone or email and then requested to provide consent before participation in the study. Recruitment staff will be responsible for providing details regarding this RCT to the patients and enrolling participants for the study. Healthy individuals who meet the study criteria will be invited to the South China Research Center for Acupuncture and Moxibustion, while patients with post-stroke hemiplegia who meet the enrolment criteria will be invited to the Guangdong 999 Brain Hospital to participate in the study.

### Inclusion criteria

Healthy individuals who meet the following inclusion criteria will be eligible to participate in this study: (1) age between 18 and 65 years, male or female sex; (2) good health and no history of stroke; (3) normal physical examination results; (4) normal results on the Mini-Mental State Examination (MMSE; a measure of cognitive impairment); (5) a body mass index (BMI) between 18.5 and 24 kg/m^2^; and (6) willingness to sign the informed consent form.

The inclusion criteria for patients with post-stroke hemiplegia will be as follows: (1) conformance with the diagnostic criteria proposed in the *Guidelines for Diagnosis and Treatment of Common Internal Diseases in Chinese Medicine Diseases of Modern Medicine* (ZYYXH/T19-2008) and the *Guidelines for the diagnosis and treatment of acute ischemic stroke in China 2018*; (2) stroke history of no more than 6 months; (3) age between 18 and 75 years, with no limitations related to sex; (4) Fugl-Meyer assessment (FMA) score less than 95 points for the right limb, muscle strength of the right limb less than Grade 4, and FMA score and muscle strength of the left limb within the normal range; (5) consent to undergo acupuncture; (6) adequate consciousness, stable vital signs, no obvious mental retardation, no obvious obstacles in hearing, MMSE score within the normal range (normal thresholds: illiteracy, > 17 points; elementary school, > 20 points; junior high school and above, > 24 points), and ability to undergo basic procedures such as rehabilitation training; and (7) willingness to participate in the study and sign the informed consent form.

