### Randomisation and allocation concealment

A total of 80 healthy participants and 40 patients with post-stroke hemiplegia will be recruited. The 80 healthy participants will be randomised 1:1:1:1 to 2-Hz, 50-Hz, 100-Hz, and sham electroacupuncture groups. The 40 patients with post-stroke hemiplegia will be randomised 1:1 to an opposing needling group or a conventional treatment group. Randomisation will be performed by the Package for Encyclopedia of Medical Statistics 3.1 software (West China School of Public Health, Sichuan, China) and will be overseen by an independent statistician. Healthy participants will be sequentially assigned a random number from 1 to 80, and patients with post-stroke hemiplegia will be sequentially assigned a random number from 1 to 40. Opaque sealed envelopes will be numbered consecutively with a serial number on the outside for randomisation and will contain the allocation information. The envelope will be opened when the participant or patient enters the trial after providing informed consent. Healthy participants will then be allocated to one of the four groups and the patients will be allocated to one of the two groups. All participants and patients will receive an intervention according to their group allocation. The random allocation sequence and the opaque sealed envelopes will be kept by two independent researchers.

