### Electromyography (EMG) measurement

RMTs and MEPs induced by TMS will be recorded from bilateral thenar muscles. Surface electrodes will be used to record the RMTs and MEPs of the thenar muscles and placed on the skin over the thenar muscles after skin disinfection. The surface recording electrodes will be placed bilaterally on each side of the thenar muscles, and the reference electrodes will be placed directly next to them (1 cm). Two ground wire disc electrodes will be placed on the upper edge of radius styloid process to reduce interference to the EMG signal. All electrodes will be checked every 15 min to ensure that they are in good contact with the skin and underlying muscles.

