#### For patients

All patients with post-stroke hemiplegia will receive conventional treatment according to the *Guidelines for the diagnosis and treatment of acute ischemic stroke in China* 2018 [28], which includes active control of blood pressure and blood sugar level, nutritional support, administration of the neurotrophic drug citicoline sodium 0.1~0.2 g, three times a day, orally; and statin treatment if considered necessary by the clinician. The patients will receive the anticoagulant aspirin 0.15~0.30 g, once a day, orally, and patients who cannot tolerate aspirin will receive clopidogrel instead. The patients will also receive basic rehabilitation training, including physical therapy, occupational therapy, and additional training as appropriate, e.g., weight loss support training or isokinetic muscle training. In addition, patients who suffered from the right side of the affected limb due to post-stroke hemiplegia in the opposing needling group will receive electroacupuncture on the left side of the unaffected limb in total 10 times (once per day for 5 consecutive days followed by a 2-day break altogether 2 weeks.) The acupoints and the operation method of electroacupuncture were described as the healthy participants in electroacupuncture groups. The electroacupuncture frequency will be the optimal frequency acquired from the healthy participants in electroacupuncture groups and the intensity will be set to the maximum-tolerated intensity for each patient and the time will sustain 20 min. Besides, the patients in the conventional treatment group will receive sham opposing needling intervention on the left side of the unaffected limb in total 10 times. The course of treatment will be the same as the patients in the opposing needling group. The operation method of sham electroacupuncture was also described as the healthy participants in sham electroacupuncture groups.

To maintain study fidelity, all researchers will receive training on the study methods, techniques, and study monitoring. All research staff will be tested after training to ensure they can consistently replicate the protocol.

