### Outcome measures

#### Primary outcome measure

The primary outcome measure will be the per cent change in the RMTs of the thenar muscles at baseline and after the intervention. The RMTs of the thenar muscles will be delivered by a TMS pulse every 30 s bilaterally to the left or right M1, respectively, for 10 pulses in the fully relaxed state. The MEP of the thenar muscles should be greater than or equal to 50 μV for at least half (5/10) of the TMS pulses. The RMT is defined as the minimum intensity that is needed to elicit the MEP ≥ 50 μV in at least 50% of the pulses.

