### Biomarkers for predicting upper limb motor function after stroke

Upper limb motor function is difficult to predict in stroke survivors. One clinical study pointed out that the FMA may be used as a tool to define motor recovery and guide the choice for therapy, and patients who fit that model showed a fixed proportional upper extremity motor recovery of about 78%. However, this proportional recovery model was seriously challenged by some severe types of stroke [48]. Researchers are still struggling to explain these different patterns of stroke recovery. Thus, the development and implementation of biomarkers in stroke recovery research are difficult. During the acute phase after stroke, even at the maximum stimulation in TMS, the affected hemisphere often fails to induce MEPs. In patients with preserved MEPs, the MEPs are smaller and motor thresholds are generally higher than those recorded from unaffected hemispheres or healthy individuals. Within the first few months, MEPs may reappear again and gradually increase, and the RMTs of the affected hemisphere tends to decrease [49–53]. Some studies have reported that TMS measures correlate with the long-term functional outcome, such as corticospinal tract integrity evaluated early after stroke [50], and that improvements in TMS measures reflect improvement in corticospinal integrity during the first few months of recovery [54]. Stinear proposed the ‘PREP algorithm’, an important component of which is the presence or absence of MEPs in arm muscles within the first week after stroke, which, in combination with the TMS response, clinical upper limb strength measures, and MRI measures of corticospinal tract asymmetry, can predict the recovery prospects for individual patients [31, 55–57]. For the RMTs of the unaffected hemisphere, the meta-analysis by McDonnell found no differences compared to healthy controls, regardless of the stage of stroke [56]. Catano found no obvious correlation between RMTs changes and lesion location [51]. In contrast, Charlotte Rosso conducted a systematic review of relevant studies and found a correlation between RMTs and upper limb motor function after stroke, indicating that RMTs may be regarded as a potential biomarker of post-stroke upper limb motor function [57]. Thus, it is possible to regard MEPs and RMTs as suitable biomarkers for predicting post-stroke upper limb function.

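### Time since stroke onset, prognostic for affected-side RMT by the protocol's own account, is neither stratified for nor adjusted for in the patient comparison; this costs precision and leaves chance imbalance uncorrected, but is not a bias.

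*Protocol article*

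**What the plan says.** All places are in the protocol article.

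- **Inclusion criteria**, patients, criterion 2: "stroke history of no more than 6 months". Only the upper end is fixed.
- **Biomarkers for predicting upper limb motor function after stroke**: "Within the first few months, MEPs may reappear again and gradually increase, and the RMTs of the affected hemisphere tends to decrease". For the unaffected hemisphere, the same section cites a meta-analysis that "found no differences compared to healthy controls, regardless of the stage of stroke".
- **Electromyography (EMG) measurement**: "RMTs and MEPs induced by TMS will be recorded from bilateral thenar muscles". **Primary outcome measure** then states: "The primary outcome measure will be the per cent change in the RMTs of the thenar muscles at baseline and after the intervention". Nothing there limits it to one side.
- **Randomisation and allocation concealment**: "The 40 patients with post-stroke hemiplegia will be randomised 1:1 to an opposing needling group or a conventional treatment group", and "patients with post-stroke hemiplegia will be sequentially assigned a random number from 1 to 40". No stratification factor is named.
- **For patients**: the control is concurrent and on the same schedule, since "the patients in the conventional treatment group will receive sham opposing needling intervention on the left side of the unaffected limb in total 10 times". Treatment runs over two weeks.
- **Statistical analysis**: the patient comparison is an independent t test, or a Wilcoxon rank-sum test if the data are not normal. Neither takes a covariate.

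**The concern.** Patients soon after onset and patients close to month 6 enter the same comparison. On the protocol's own description they should differ in how much the affected-side RMT moves over two weeks without needling. That has two consequences.

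First, the mix of early and late patients adds outcome variance that a recorded variable could remove. Second, with 20 per arm the two arms can differ by chance in their share of early patients. The unadjusted estimate then carries part of that difference, which may make needling look better or worse than it is.

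Stratification is a property of the allocation list, so a later analysis plan cannot supply it. For the analysis, the article does more than stay silent: it names tests that leave this variable out.

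**Working it through.** **Inputs from Sample size calculation.** Difference 3.57, SD 3.67, two-sided alpha 0.05 (Z = 1.96), power 80% (Z = 0.84), 10% dropout, 18 evaluable and 20 recruited per arm.

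**Assumptions, not in the documents.** The share of early patients, the distribution of onset times, and the share R² of the variance in RMT change that time since onset explains (10%, 25%, 40%). The SD of 3.67 is taken as the SD of RMT change.

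**1. The plan's own figure.** The usual two-sample formula gives 2 × [(1.96 + 0.84) × 3.67 / 3.57]² = 2 × 8.29 = 16.6, so 17 per arm. Exact t-test power is 78.5% at 17 and 80.9% at 18. So 18 is right for a t test, and 18 / 0.90 = 20. (The printed formula lacks the factor 2, which is a separate matter.)

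**2. Chance imbalance at 20 v 20.**
- If exactly 20 of the 40 are early, the number in one arm is hypergeometric(40, 20, 20). P(12 v 8 or worse) = 0.343; P(13 v 7 or worse) = 0.113.
- If each patient is instead early independently with probability one half, the arms differ by 20 percentage points or more in 27% of randomisations and by 30 points or more in 8%.
- If onset times are uniform over 0 to 6 months, their SD is 6/√12 = 1.73 months, and the SD of the difference in arm means is 1.73 × √(2/20) = 0.55 month. The difference exceeds 1 month in about 7% of randomisations.

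**3. What an imbalance does to the estimate.** With equal early and late classes a gap D apart in spontaneous change, R² = (D/2)² / 3.67², so D = 2 × 3.67 × √R². A 12 v 8 split shifts the estimate by D × 4/20. With uniform onset times, a 1-month difference in means shifts it by 3.67 × √R² / 1.73.

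| R² | D | shift at 12 v 8 (share of 3.57) | shift at 1 month (share of 3.57) |
|---|---|---|---|
| 10% | 2.32 | 0.46 (13%) | 0.67 (19%) |
| 25% | 3.67 | 0.73 (21%) | 1.06 (30%) |
| 40% | 4.64 | 0.93 (26%) | 1.34 (38%) |

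The standard error of the difference is 3.67 × √(2/20) = 1.16. The shifts can go either way and average zero over randomisations.

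**4. Error rate and power.** Simulation with 18 per arm and uniform onset times gives these results:

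- Unadjusted type I error over all randomisations is 5.2%, 4.9% and 5.0% at the three values of R². Adjusted, it is about 5%.
- In the roughly 8% of randomisations where mean onset time differs by more than 1 month, unadjusted type I error is 9%, 15% and 22%. Adjusted, it stays at about 5%. In the rest, the unadjusted rate falls slightly below 5%.

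For power, the residual SD after adjustment is 3.67 × √(1 − R²). Noncentral t power at 3.57 with 33 degrees of freedom is:

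| R² | residual SD | adjusted power |
|---|---|---|
| 10% | 3.48 | 85% |
| 25% | 3.18 | 90% |
| 40% | 2.84 | 96% |

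Unadjusted power is 81%. The simulation, which also charges for chance imbalance in the covariate, gives 84%, 90% and 95% adjusted. If onset time explains nothing, adjusted power is about 80%.

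**The case against.** The strongest reply is that nothing here is biased. Allocation is random, the sham control is concurrent, and background treatment is the same in both arms, so spontaneous recovery falls on both. Chance imbalance is already covered by the 5% error rate, as the simulation confirms, and any unstratified prognostic factor in 40 patients could be raised in the same way. This stands as an answer to a claim of bias. It does not answer the loss of precision, and this factor differs from others in that the protocol itself ties it to the course of the primary outcome.

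A second reply is that the spontaneous fall is described only for the affected hemisphere and the early months, in hedged terms, while unaffected-side RMT is reported as similar to healthy controls whatever the stage. That also stands and limits the point. It does not remove it, because both sides are measured and the primary outcome is not restricted to the unaffected one.

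A third reply is that the other entry criteria (stable vital signs, ability to undergo rehabilitation training) exclude some very early patients, and that covariates are often left to an analysis plan, which is not shown here. The first part narrows the window without closing it. The second carries some weight for the model, but none for the stratification of the list.

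A reader might also infer that spontaneous decline imitates the expected treatment effect because the sample size section speaks of RMT reductions. That wording belongs to the healthy-participant calculation. The patient calculation gives 3.57 without a direction.

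**Conclusion.** The point holds as one of precision and of protection against chance imbalance. By the protocol's own account time since onset is prognostic, at least for affected-side RMT. It is already needed to check eligibility, yet it is used neither in the allocation nor in the named tests. The gain from using it is about 81% to 85%, 90% or 96% power if it explains 10%, 25% or 40% of the variance.

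Those shares are assumptions, because the documents give no rate of RMT change. The planning figures are also in RMT units while the primary outcome is a per cent change, so the sizes are indicative. Much larger distortions are not credible: an early-versus-late gap of 6 units over two weeks would alone account for (6/2)² / 3.67² = 9 / 13.47 = 67% of the planning variance.

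A reader might conclude that recovery stage can pass for a needling effect and that the design is confounded. The documents do not support that: an imbalance can hide an effect as easily as mimic one, and the overall error rate is held.

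**What to change.** Replace the unadjusted patient comparison in Part 2 with a prespecified linear model of RMT change, as the protocol defines that change, on arm with time since onset as a covariate. Fix the form of the covariate before unblinding. The onset date is already needed for criterion 2. The rank-sum test can stay as a sensitivity analysis.

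If recruitment allows, also split the patient list into two onset-time strata with a cut-point set in advance, using blocks of varying size within each stratum. If recruitment is too far advanced, the covariate alone gives most of the benefit.

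Cost: one degree of freedom, about one percentage point of power if onset time turns out not to matter (81% to 80%), and a second envelope series if the list is stratified. No extra patients, visits or measurements are needed.
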